### **7.2 Secondary endpoints**

The following groups of subjects will be characterized:

- Subjects with positive SARS-CoV-2 antigen result test at the Ag-RDT screening
- Subjects with negative SARS-CoV-2 antigen result test at the Ag-RDT screening
- Subjects with negative SARS-CoV-2 antigen result test at the Ag-RDT screening with a positive test on SARS-CoV-2 after attending the festival.
- Subjects with negative SARS-CoV-2 antigen result test at the Ag-RDT screening without a positive test on SARS-CoV-2 after attending the festival.

For each group, the following characteristics will be described:

- Gender
- Age
- Place of residence
- Vaccination level (vaccine received, number of doses, date of vaccination)
- Reinfection status (date of previous SARS-CoV-2 infection, if any)
- Number of days attending the festival
- Days of attendance to the festival

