### 3 RATIONALE

The importance of the live events industry to the economy is significant. However, the public health response to COVID-19 led to an unprecedented closure in the entertainment industry. Although substantial advances have been made to re-open other industries, there has been limited experience on the reopening of live events such as live music concerts, festivals, or congresses. Because these experiences require people to be very close together, live events generally create conditions that favour virus transmission. Thus, preventive measures need to be adopted. However, there are no clear policy protocols to permit the return of live entertainment at full capacity.

Several self-care and risk mitigation strategies are currently being used.

On the one hand, facemasks wearing, handwashing, and capacity reduction to promote social distancing are non-pharmaceutical interventions available to reduce the basic reproduction rate of the virus.

Infection or immunity passports, which refer to tests that demonstrate negative infection status or immunity have also been used to re-open activities such as travelling.

Finally, given the continued roll out of vaccinations, vaccine passports have become a new criterion to demonstrate immunity in certain activities.

How to combine all these strategies in a cost-efficient manner to celebrate safely live events is still under debate.

On July 3, 2021, CanetRock music festival took place in Canet, a town located 40 km north-east of Barcelona, Catalonia, Spain. On July 8, 9 and 10, 2021, Cruïlla music festival took place in Barcelona, Catalonia, Spain. To reduce the risk of SARS-CoV-2 transmission within the festival, the organizers applied the following measures.

- Attendees to the festival were screened for SARS-CoV-2 infection with Antigen Rapid Diagnostic Test (Ag-RDT) via a nasopharyngeal swab.
- Non-contact body temperature screening was performed.
- Attendees were given a certified Filtering facepiece 2 (FFP2) mask. The use of the mask was compulsory whenever people were not eating/drinking.

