This study aims to compare the prevalence of COVID-19 among those attending the Cruïlla festival and a control cohort, before and after attending the festival. Independently, it will also compare the prevalence of COVID-19 among those attending the CanetRock festival and its corresponding control cohort, before and after attending the festival. We will also characterize the subjects developing or not COVID-19 within 14 days after attending the festival. This characterization will be specially focused on the socio-demographic characteristics of the attendees (age, gender, geographic location), the individual level of COVID-19 immunity (based on vaccination and/or previous infections) and the behaviour at the festival (number of days attended, and days of attendance).

Catalan Health Department (*Conselleria de Salut, Generalitat de Catalunya*) has sponsored this study in collaboration with [name] from the *Hospital Germans Trias i Pujol* and the *Fundació Lluita contra la Sida*, the Cruïlla Barcelona Festival and the CanetRock Festival. This analysis will provide information regarding the

effectiveness of preventive measures against COVID-19 transmission taken during the festivals, which will be beneficial for the organization of future events.

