### **4.2 *Secondary objective***

Characterization of subjects according to development or not of COVID-19 within 14 days after attending the festival.

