### ***6.2 Observation period***

Data regarding the number of SARS-CoV-2 positive test results in each cohort will be collected considering 14 days before and 14 days after the festival (24th June - 24th July).

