## **7 VARIABLES AND MEASURE INSTRUMENTS. MEASUREMENTS DEFINITION AND DESCRIPTION**

### **7.1 Primary endpoint**

To study the prevalence of Covid-19 among those attending the festivals, the following endpoint will be analysed:

- Frequency of subjects attending to the Cruïlla festival who report a positive test on SARS-CoV-2 within the 14 days after the festival.
- Frequency of subjects attending to the CanetRock festival who report a positive test on SARS-CoV-2 within the 14 days after the festival.
- Frequency of subjects in each control cohort who report a positive test on SARS-CoV-2 within the 14 days after the festival.

Additional analysis will be performed excluding the following subjects, who will be considered as not infected during the festivals:

- Subjects who tested positive on SARS-CoV-2 6 days after their last day attending the festival.
- Subjects who tested positive within 2 days after attending the festival.

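### Section 7.2 omits the 14-day limit of the secondary objective, and the single date range in section 6.2 does not reliably supply it

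*Protocol*

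**What the plan says.** The secondary objective in protocol section 4.2 reads "Characterization of subjects according to development or not of COVID-19 within 14 days after attending the festival". The Rationale (section 3) repeats the limit: "We will also characterize the subjects developing or not COVID-19 within 14 days after attending the festival".

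Section 7.2 turns this objective into groups. Its third and fourth groups are attendees with a negative screening test who are, respectively, "with a positive test on SARS-CoV-2 after attending the festival" and "without a positive test on SARS-CoV-2 after attending the festival". Neither carries a time limit. Section 7.1, immediately before, does state one in each of its three bullets: subjects "who report a positive test on SARS-CoV-2 within the 14 days after the festival".

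Section 6.2 limits the collection of positive results to "14 days before and 14 days after the festival (24th June - 24th July", with one pair of dates for both festivals. The festivals were on different dates: "On July 3, 2021, CanetRock music festival took place in Canet" (section 3), and the same section places Cruïlla on 8, 9 and 10 July. Section 6.3 has Cruïlla attendees exposed for one, two or three days and CanetRock attendees for one day. Section 7.2 lists the number of days and the particular days attended among the characteristics to be described for each group. Section 8.2 refers the analysis of the endpoints back to their description in section 7.

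**The concern.** Section 8.2 makes section 7 the operative definition, so an analyst who follows it would apply the open wording of 7.2 and not the limit in 4.2. Case status would then depend on where the data extract happens to stop, and the extract stops at different distances from each festival and each Cruïlla day.

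Two things are at stake. The secondary case group may not measure the stated objective, and for CanetRock it may not agree with the 14-day primary endpoint in 7.1. Within Cruïlla, the time available to become a case would vary with the last day attended. Because days of attendance are themselves described for cases and non-cases, and the Rationale names behaviour at the festival as a special focus, a small difference by attendance pattern could appear with no true difference in risk.

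**Working it through.** **Inputs.** CanetRock 3 July; Cruïlla 8, 9 and 10 July (section 3). Data range 24 June to 24 July, described as 14 days on each side (6.2). Limit of 14 days after attending (4.2 and section 3). No limit in 7.2.

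**Step 1: reproduce the range in 6.2.** Window = first festival day − 14 to last festival day + 14.
- Cruïlla: 8 July − 14 = 24 June; 10 July + 14 = 24 July. The stated range is reproduced exactly.
- CanetRock: 3 July − 14 = 19 June; 3 July + 14 = 17 July. It is not reproduced. The stated range starts 5 days late and ends 24 − 17 = 7 days late.

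**Step 2: follow-up if 7.2 is read literally and data run to 24 July.** Follow-up = 24 July − last day attended.

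| Last day attended | Follow-up (days) | Ratio to 14 | Share of follow-up beyond day 14 |
|---|---|---|---|
| CanetRock, 3 July | 21 | 1.50 | 7/21 = 33% |
| Cruïlla, 8 July | 16 | 1.14 | 2/16 = 12.5% |
| Cruïlla, 9 July | 15 | 1.07 | 1/15 = 6.7% |
| Cruïlla, 10 July | 14 | 1.00 | 0 |

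Anyone who attended all three Cruïlla days has 10 July as last day, so follow-up length is linked to the number of days attended as well as to which days.

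**Step 3: follow-up if the words of 6.2 govern.** CanetRock data end on 17 July, so follow-up there is 14 days. Cruïlla data still end on 24 July, and the spread of 14 to 16 days stays.

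**Step 4: what it could do to the risk.** The protocol gives no incidence. Assume a constant daily probability r of a positive test; the cumulative risk over k days is 1 − (1 − r)^k.

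| Assumed r | 14 days | 16 days | 21 days |
|---|---|---|---|
| 0.05% | 0.70% | 0.80% | 1.04% |
| 0.1% | 1.39% | 1.59% | 2.08% |
| 0.2% | 2.76% | 3.15% | 4.12% |

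Across this range, 16 days gives about 1.14 times the 14-day risk and 21 days about 1.5 times.

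**Step 5: check candidate corrections.**
- Limit of 14 days counted from the end of the festival: CanetRock has 14 days, but Cruïlla attendees still have 14 to 16 days from their own last day.
- Limit of 14 days counted from each attendee's last day: follow-up ends on 17 July (CanetRock) and on 22, 23 or 24 July (Cruïlla). Everyone has 14 days, and all four dates lie inside the stated range.

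**The case against.** The best defence is that the limit is stated elsewhere and carries over. Section 4.2, which 7.2 implements, says 14 days; so do the Rationale, the Design section (1.7), 7.1 and the words of 6.2. No section gives a different limit for 7.2, whose wording can be read as shorthand for 4.2. The intention is clear, and this argument makes the point smaller. It does not remove it: 8.2 refers the analysis to section 7, and the calendar dates in 6.2 contradict their own 14 days for CanetRock, so the data range cannot be relied on to impose the limit.

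A reader might infer that 7.2 by itself gives attendees 14 to 21 days of follow-up, that a third of CanetRock secondary cases will miss the objective, and that this will produce a spurious association with day of attendance. The documents do not support that reading:
- The 21 days need both the open wording of 7.2 and the dates of 6.2 overriding the words of 6.2.
- The one third is a share of follow-up time. It becomes a share of cases only under constant incidence, which the protocol does not state.
- The festivals are analysed independently and CanetRock lasted one day, so day of attendance cannot vary there, and a difference between festivals does not enter any comparison of attendance days.
- The Cruïlla spread would persist if the 14-day wording of 7.1 were simply copied into 7.2 and counted from the end of the festival. Its source is also the unstated starting point.
- Section 8.2 foresees frequencies and percentages for the endpoints, with no test or model of attendance day.

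Window conventions are often settled in an analysis plan. Here, however, the protocol itself fixes the groups, and does so differently from its objective.

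**Conclusion.** The point holds in limited form. The groups in 7.2 omit a limit that 4.2 and the Rationale set, and 6.2 supplies it for Cruïlla as a festival but not dependably for CanetRock. The size depends on how 6.2 is read. If its dates govern, CanetRock cases are counted over 21 days instead of 14. If its words govern, only the Cruïlla spread of 14 to 16 days remains, at most 1.14 times, and it applies in full only to those whose sole day was 8 July, a number the protocol does not give. In that case the consequence is a modest shift in descriptive secondary tables. The day counts follow from the protocol's dates alone; every statement about risk or share of cases rests on the assumed constant incidence. The primary endpoint states its 14 days and does not share the missing limit, but it shares the question of where the count starts.

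**What to change.** Three changes belong together.

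1. In 7.2, define the third and fourth groups as with or without a positive SARS-CoV-2 test within 14 days after the attendee's last day attending. The additional analysis in 7.1 already counts from the last day attended for one of its exclusions.
2. In 6.2, give each festival its own window: CanetRock 19 June to 17 July, Cruïlla 24 June to 24 July.
3. Use the same starting point in 7.1, or state that the two differ. Otherwise, if 7.1 counts from the end of the festival, a Cruïlla attendee whose only day was 8 July and who tested positive on 23 or 24 July would be a primary case and a secondary non-case.

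The cost is mainly wording. Attendance days are planned variables, and the exclusions in 7.1 already need test dates. The secondary tables would have slightly fewer cases. If 7.1 is moved to the last day attended, each control needs the date of its paired attendee. Because 7.3 describes control results as aggregated, that date would have to be applied before aggregation; if this is not practical, stating the difference in starting points is the cheaper choice.

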### **7.3 Data collection**

Ag-RDT result, and demographics, of the attendees was collected by Cruïlla Festival and the CanetRock Festival, after the individuals agreed to data capture for epidemiological and research purposes.

Data regarding vaccination status, and positive SARS-Cov-2 test of the attendees at the festival and the control group will be collected from the Catalan Health Department registry.

In addition to the data about the subjects who attended the festival, the following data will be used for the study:

- Number of subjects that purchased an entrance, who tested positive for SARS-CoV-2 before the festivals and returned their entrance (without participating in the Ag-RDT screenings nor attending the festivals).
- Aggregated results of SARS-CoV-2 tests for the control cohort, for the complete cohort and subdivided according to their COVID-19 immunity status.

## **8 STATISTICAL ANALYSIS**

After the validation of the database, its content will be transferred to datasets for statistical analysis. All statistical analyses will be performed using the statistical package R 3.6.3.

### ***8.1 Populations for the analyses***

Analysis will be performed using the Full Analysis Set (FAS) population, which will include all subjects who underwent SARS-Cov-2 antigen test within the Cruïlla festival. An independent analysis will be done using again the Full Analysis Set (FAS) population, including all subjects who underwent SARS-Cov-2 antigen test within the CanetRock festival. Those for whom information about their Covid-19 vaccination status is available at the Catalan Health registry will be paired with a control subject and included in the analysis.

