### ***1.10 Type of population and number subjects***

Study population will be subjects who underwent SARS-Cov-2 antigen test within the Cruïlla festival or the CanetRock Festival, and who are registered at the Catalan Public Health System. Overall, 40000 people underwent SARS-Cov-2 antigen test within the Cruïlla festival. For the CanetRock Festival, 22000 people underwent SARS-CoV-2 antigen test before attending the festival. The study will also include data from a control cohort, made of subjects that did not attend the event but were paired with the attendees. Pairing will be made 1:1 based on age, gender, geographical area and Covid-19 immune status (vaccine/previous infection).

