### ***6.3 Treatment and exposure description***

For the Cruïlla Festival cohort, subjects with negative results at the SARS-Cov-2 Ag-RDT screening were exposed to the Cruïlla festival for 1, 2 or 3 days.

For the CanetRock Festival cohort, subjects with negative results at the SARS-Cov-2 Ag-RDT screening were exposed to the CanetRock festival for 1 day.

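### The analysis set is everyone antigen-tested, but section 6.3 describes only screen-negatives as exposed, so a screen-positive's later positive can count as a post-festival case

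*Protocol*

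**What the plan says.** **Analysis set.** Protocol section 8.1 defines the Cruïlla set as one "which will include all subjects who underwent SARS-Cov-2 antigen test within the Cruïlla festival" and the CanetRock set as one "including all subjects who underwent SARS-Cov-2 antigen test within the CanetRock festival". Section 1.10 agrees: "Study population will be subjects who underwent SARS-Cov-2 antigen test within the Cruïlla festival or the CanetRock Festival". Sections 6.1 and 6.5 also define the population by having been tested. The further condition in 8.1 concerns registry data, not the screening result: "Those for whom information about their Covid-19 vaccination status is available at the Catalan Health registry will be paired with a control subject".

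**Exposure.** Section 6.3 says that "subjects with negative results at the SARS-Cov-2 Ag-RDT screening were exposed to the Cruïlla festival for 1, 2 or 3 days" and that "subjects with negative results at the SARS-Cov-2 Ag-RDT screening were exposed to the CanetRock festival for 1 day". It says nothing about people who screened positive.

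**Primary endpoint.** Section 7.1 gives it for Cruïlla as "Frequency of subjects attending to the Cruïlla festival who report a positive test on SARS-CoV-2 within the 14 days after the festival", with parallel items for CanetRock and for the control cohorts. None of these items requires a negative entry screen.

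**Secondary description.** Section 7.2 lists "Subjects with positive SARS-CoV-2 antigen result test at the Ag-RDT screening" as a group to be characterised, so screen-positives are study subjects.

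**The concern.** The population that is analysed and the population described as exposed are not the same. Following 8.1 literally puts screen-positives in the attendee denominator. If one of them has a further positive registered in the 14 days after the festival, such as a confirmatory or repeat test, nothing in 7.1 clearly keeps it out of the numerator.

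That matters for how the result is read. Section 3 says the study will inform on how well the preventive measures worked, and entry screening is the first measure it lists. An infection found at the entry screen, and so present before any exposure, could appear in the results as a post-festival case. Success of the screen would then look like transmission at the event.

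**Working it through.** There is no planned figure to reproduce. Section 6.5 states that no formal sample size calculation was made, and its 40000 and 22000 are counts of people tested. The check therefore compares definitions and then illustrates the possible size.

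**1. Does any wording remove screen-positives from the primary count?**

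- *Section 8.1:* no. The screening result is not a condition.
- *Section 7.1, the word attending:* not reliably. Section 3 says that attendees were screened, which covers everyone tested. Section 1.7 pairs each attendee with a control, while section 6.5 pairs those who were tested and are registered. Where the authors want a screen-negative condition they write it, as in the last two groups of 7.2; 7.1 has none.
- *Section 7.1, early-positive exclusion:* no. Removing positives within 2 days applies only to an additional analysis. It is timed from attendance, which is undefined for someone who did not enter. A repeat positive falling between the 2-day and 6-day cut-offs would stay in even there.

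**2. How large could the effect be?**

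None of these inputs is in the protocol; all are assumptions.

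- s = share of tested subjects who screen positive: 0.1% to 1%
- c = share of screen-positives with a registry positive in the 14 days after: 10% to 90%
- p = 14-day risk in screen-negatives: 0.5% to 2%

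Formulas:

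- Frequency in all tested = (1 − s)p + sc
- Multiplier against screen-negatives only = (1 − s) + sc/p
- Share of counted cases that are screen-positives = sc / [(1 − s)p + sc]

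| Case | s | c | p | Multiplier | Share of cases |
|---|---|---|---|---|---|
| Low | 0.1% | 10% | 2% | 0.999 + 0.005 = 1.004 | 0.5% |
| Middle | 0.5% | 50% | 1% | 0.995 + 0.250 = 1.245 | 20.1% |
| High | 1% | 90% | 0.5% | 0.990 + 1.800 = 2.79 | 64.5% |

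Counts in the middle case, taking everyone tested as registered:

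- Cruïlla: 40000 × 0.005 = 200 screen-positives and 200 × 0.5 = 100 added cases. Screen-negatives give 39800 × 0.01 = 398. The frequency is 498/40000 = 1.245%, against 1.000%.
- CanetRock: 22000 × 0.005 = 110 screen-positives and 55 added cases. Screen-negatives give 21890 × 0.01 = 218.9. The frequency is 273.9/22000 = 1.245%, against 1.000%.

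The multiplier exceeds 1 whenever c exceeds p. It does not depend on the number tested.

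**The case against.** The best defence is that the Full Analysis Set is deliberately wide, because 7.2 needs the screen-positives, and that section 7 then narrows the primary endpoint. The objective and 7.1 both speak of those attending. Section 8.2 analyses endpoints by group as set out in section 7. Section 7.2 splits only screen-negatives by a later positive. Section 7.3 also treats being screened and attending as separate acts when it describes ticket holders who did neither. On this reading, post-festival cases are counted among screen-negatives.

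This is a fair reading and may be what was intended, but it does not close the point. It gives the primary endpoint a different denominator from the set in 8.1, and no sentence says so.

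Three stronger inferences are tempting but are not supported:

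- *That screen-positives will be counted as cases.* The text allows it but does not require it. It takes both treating them as attending and a further positive registered in the window, and the protocol does not say how often they were retested.
- *That the protocol says only screen-negatives were exposed, or that positives were turned away.* Section 6.3 describes screen-negatives as exposed; the word only is not there, and no passage states that entry was refused. Non-exposure is a reasonable inference from 6.3.
- *That the comparison with controls is biased by a known amount against attendees.* Controls had no entry screen, so undetected current infections remain among them. The net direction of the comparison is not established.

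**Conclusion.** The point holds as a conflict between definitions. Sections 1.10, 6.1, 6.5 and 8.1 analyse everyone tested, section 6.3 describes screen-negatives as exposed, and 7.1 does not say which of the two its endpoint uses. People not described as exposed are in the analysed set, and later registry positives of theirs can be counted as post-festival cases.

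The attendee frequency is biased upward to the extent that this happens. Under the assumed ranges the multiplier runs from about 1.00, which is negligible, to 2.79, with 1.245 in the middle case. These figures show sensitivity to unknown rates and are not an estimate of the bias. If screen-positives seldom have a later registered positive, the effect is small. Because the conflict affects both numerator and denominator of the primary endpoint, it should be settled before the data are analysed.

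**What to change.** Reconcile sections 6.3, 7.1 and 8.1, for each festival:

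- State that the primary post-festival endpoint is analysed in registered subjects with a negative Ag-RDT who entered, together with their paired controls.
- Keep screen-positives for the 7.2 description only.
- State that the entry Ag-RDT, and any test confirming it, is not a post-festival event.
- Apply a parallel rule to controls, using the pre-festival registry positives that section 6.2 already collects. Report the asymmetry that remains as a limitation, or show the comparison in all tested subjects as a sensitivity analysis.

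**Cost.** The change is mainly wording, since section 7.3 shows that the Ag-RDT result is already collected. The analysed number falls slightly. The restriction takes detected current infections out of the attendees only, and registry positives cannot fully stand in for an entry screen among controls; this is why the limitation has to be stated.

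Two practical points need checking. Section 7.3 foresees aggregated test results for controls, so the control-side rule may have to be applied by the health department before aggregation. The dates in 6.2 start on 24 June, which is 14 days before Cruïlla opened on 8 July but only 9 days before CanetRock on 3 July, so the pre-festival window for CanetRock controls should be confirmed.
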